However, there are no previous studies that have analyzed the effects of a multidomain program on healthy middle-aged and older adults with interventions of less than one year, which could help make implementation more feasible and reduce drop-out rates [25]. Furthermore, no previous research has examined the effects of a multidomain intervention conducted outdoors, even though outdoor exercise interventions are expected to become pivotal in interventions to improve the health of older people [26].

Consequently, the aim of this protocol is to conduct a preliminary study that explores the effects of an 18-week, twice-weekly outdoor multidomain intervention—including physical exercise, cognitive stimulation, and social engagement—on the health of late middle-aged and older adults. This study also seeks to assess the feasibility and acceptability of the intervention, thereby informing the design of future large-scale trials by evaluating both its potential effects and feasibility. Additionally, this study aims to assess the feasibility and acceptability of the ACTIVA intervention among older adults, to inform future larger-scale trials. We hypothesize that the ACTIVA-Senior program, conducted entirely in an open-air environment, will lead to significant improvements in cognitive, physical, and psychological outcomes. Moreover, the outdoor setting may contribute to greater adherence, enhanced social interaction, and a more enjoyable and relaxed experience, potentially amplifying the overall impact of the intervention on the participants.

This protocol describes a single-blind randomized controlled trial designed as a preliminary and exploratory study. Its dual aim is to evaluate the feasibility and acceptability of an outdoor multidomain intervention for late middle-aged and older adults and to examine its initial effects on cognitive, physical, and psychological health outcomes.

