### 2.9. Statistical Analysis

The qualitative data from sociodemographic questionnaires will be summarized using frequencies, while the rest of the quantitative variables will be described using the mean and SD for both the TG and CG across different assessment time points. To ensure robust statistical evaluation, Type I (alpha) error control will be prioritized, with the Bonferroni correction applied to set the threshold for statistical significance at *p* = 0.05. Group comparisons will adhere to the intention-to-treat principle, incorporating necessary adjustments for adherence to the exercise program. Missing data will be handled using multiple imputation based on fully conditional specification (FCS), performed in SPSS 25.0 using the Multiple Imputation module.

To assess baseline characteristic differences between groups, the Student’s *t*-test will be used for parametric numerical variables, the Mann–Whitney U test for non-parametric variables, and the chi-square (χ^2^) test for categorical binary variables. Changes within and between the TG and CG from baseline to follow-up assessments will be analyzed using the appropriate tests. For variables with a normal distribution, a repeated-measures analysis of variance (ANOVA) will be applied. Post hoc comparisons will utilize *t*-tests with Sidak corrections to control Type I errors. For non-parametric variables, the Friedman test will be followed by the Wilcoxon test, with the Bonferroni correction applied for multiple comparisons. Sensitivity analyses will be conducted to assess the robustness of the main results under varying assumptions, including analyses with and without imputed datasets and potential alternative modeling strategies.

All statistical analyses will be conducted using SPSS version 25.0. A *p*-value of <0.05 will indicate statistical significance, with adjustments made for multiple comparisons as described above.

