In Spain, over half of the middle-aged and older population is affected by overweightness and chronic diseases [1]. Increased engagement in physical exercise and adoption of healthy habits can lead to a 10% reduction in healthcare expenses, with every euro invested in exercise potentially saving six euros in healthcare costs [76]. Moreover, establishing a holistic and sustainable program aimed at promoting community health is vital for combating dementia and reducing dependency [77]. These findings justify the need for non-pharmacological intervention projects that investigate the effects of multidomain training programs on health in middle-aged and older adults.

However, this study has some limitations. First, conducting a randomized controlled trial aimed at modifying healthy habits and physical activity presents challenges related to participant adherence, retention, and expectancy effects. The absence of an active control group, such as a group that participates in a health education program or other types of training, may influence behavioral and quality-of-life outcomes. However, the objective in establishing this no-treatment control group will be to obtain a realistic picture of how these variables evolve without any intervention, which is usually the case in this population. In future studies, it would be necessary to incorporate such components to improve engagement, better control for expectancy, and enhance interpretability. Second, while validated questionnaires and objective tests are employed, self-reported data remain susceptible to recall and social desirability biases. Third, although the sample size was informed by effect sizes from previous multidomain interventions, the relatively small cohort may limit generalizability and increase the risk of Type II errors. Finally, given the inclusion of a healthy population and the absence of cognitive screening upon recruitment, there is a potential for a ceiling effect in cognitive outcomes, which should be considered when interpreting future results. As such, findings will have to be interpreted with caution and viewed as preliminary pending confirmation in larger trials.

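### Section 2.9 plans tests of change within and between arms but does not make the between-arm contrast decisive, so a training-group pre-post change could be read as benefit

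*Protocol article*

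**What the plan says.** The Introduction predicts that the programme "will lead to significant improvements in cognitive, physical, and psychological outcomes". It does not say relative to what.

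Section 2.9 then sets out the analysis of change:

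- The general statement is "Changes within and between the TG and CG from baseline to follow-up assessments will be analyzed using the appropriate tests".
- For normal variables: "For variables with a normal distribution, a repeated-measures analysis of variance (ANOVA) will be applied". No effect from that model (time, group or group-by-time) is singled out.
- For follow-up tests: "Post hoc comparisons will utilize *t*-tests with Sidak corrections to control Type I errors". The pairs to be compared are not given.
- For the rest: "For non-parametric variables, the Friedman test will be followed by the Wilcoxon test, with the Bonferroni correction applied for multiple comparisons".
- Student's t-test, Mann–Whitney and chi-square appear by name only in the sentence on baseline differences, which begins "To assess baseline characteristic differences between groups, the Student’s".
- A separate sentence reads "Group comparisons will adhere to the intention-to-treat principle, incorporating necessary adjustments for adherence to the exercise program".

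Section 2.6 has the control group take the same four assessments as the training group (pre-test, post-test, re-test 1, re-test 2). The Discussion explains why that group exists: "the objective in establishing this no-treatment control group will be to obtain a realistic picture of how these variables evolve without any intervention".

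**The concern.** A change from pre-test to post-test within the training group mixes the programme's effect with everything else that moves scores over about 18 weeks, such as familiarity with the Stroop, Trail Making, timed and walking tests, or season. The randomised comparison removes whatever the two arms share; a within-arm test or a main effect of time does not. A significant change in TG beside a non-significant one in CG is not a test of the difference either.

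The text leaves the choice among these open, and for non-normal variables it names only tests of change over time. A hypothesis worded as significant improvement, without a comparator, would be met by a TG pre-post result alone. If that were reported as benefit, a change that the control group also shows could be carried into the larger trials this study is meant to inform.

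**Working it through.** **Side-by-side reading.** For each type of variable, which named test of change compares the arms?

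- Normal variables: the repeated-measures ANOVA can, through its group-by-time term, but it also gives a time effect. The Sidak t-tests could be within or between arms.
- Non-normal variables: Friedman compares repeated measurements. Wilcoxon, as its follow-up, compares pairs of time points. The rank test for two independent groups, Mann–Whitney, is named only for baseline. No between-arm test of change is named.

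**Inputs from the protocol article.** 26 per group, 15% dropout, 5% Type I error and 75% power (section 2.3); four assessments (section 2.6). Completers per arm: 26 × 0.85 = 22.1, taken as 22. The total of 52 cannot be reproduced directly because no numerical effect size is given. Back-solved, 22 per arm at 75% power and two-sided 5% fits a two-group difference of about 0.8 SD (0.79 by the normal formula, 0.81 by t), and 22/0.85 = 25.9, rounded up to 26.

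**Assumptions, not in the documents.** Normal scores with SD 1, no programme effect, the same retest gain g (in SD) in both arms, pre-post correlation ρ.

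**Within-TG test.** The SD of change is √(2(1−ρ)). With g = 0.3 and ρ = 0.7:

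- SD of change = √0.6 = 0.775
- standardised change = 0.3/0.775 = 0.39
- noncentrality = 0.387 × √22 = 1.82, on 21 degrees of freedom

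The chance of a significant improvement at two-sided 0.05 is 41%. Four time points give 4 × 3/2 = 6 pairs, so the Sidak level is 1 − 0.95^(1/6) = 0.0085, and the chance is 17%.

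**Between-arm test of change.** The shared gain cancels: g − g = 0. The chance of a result favouring TG is therefore half the level: 0.05/2 = 2.5%, or 0.0085/2 = 0.4%. Over 40,000 simulated trials per setting (gains of 0.2 to 0.5, ρ = 0.7), the two-sided rejection rate at 0.05 stayed between 4.8% and 5.1%.

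**Range.** Chance that the TG pre-post test shows improvement when the programme does nothing, as unadjusted 0.05 / Sidak 0.0085:

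| Shared gain (SD) | ρ = 0.6 | ρ = 0.7 | ρ = 0.8 |
|---|---|---|---|
| 0 | 2.5% / 0.4% | 2.5% / 0.4% | 2.5% / 0.4% |
| 0.2 | 17% / 4.8% | 21% / 6.5% | 29% / 10% |
| 0.3 | 32% / 12% | 41% / 17% | 57% / 28% |
| 0.4 | 52% / 24% | 64% / 34% | 81% / 54% |
| 0.5 | 71% / 41% | 82% / 56% | 94% / 78% |

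At g = 0.3 and ρ = 0.7, the pattern of TG significant and CG not significant arises in about 24% of simulated trials unadjusted and 14% with Sidak, although the true change is identical in both arms.

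**The case against.** The other side has real substance. This is a condensed article, and naming the deciding contrast is often left to the analysis plan. The trial is a parallel randomised one, the planned analysis covers change between arms as well as within them, group comparisons are to follow intention to treat, and the ANOVA can deliver the group-by-time test. The study calls itself preliminary and asks for cautious interpretation. All of that stands, and it limits the point.

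It does not remove it. The intention-to-treat sentence does not say which contrast decides. The article goes beyond silence: it commits to within-arm testing, fixes time-point tests for non-normal variables, and words its hypothesis without a comparator.

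A reader might go further in three ways that the documents do not support:

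- One might infer that the plan ranks within-arm and between-arm results equally, or intends to claim efficacy from TG change alone. No sentence says so; the wording permits it.
- One might take 41% as the plan's false-positive rate. That figure is unadjusted, whereas section 2.9 calls for Sidak-corrected post hoc t-tests, so 17% is the closer figure. Both rest on an assumed gain and correlation.
- One might apply these figures to every outcome. Practice effects are plausible for the cognitive, timed and walking tests but not for bioimpedance or anthropometry, and the Discussion itself warns of a ceiling in cognitive scores, which would limit gains. Regression to the mean is also possible in principle, but the eligibility criteria do not select on extreme values of these tests.

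**Conclusion.** The point holds as a weakness of wording with a statistical consequence. A valid contrast is available for normal variables but is not designated; for non-normal variables no between-arm test of change is named. Under the assumed 0.3 SD shared gain, correlation 0.7 and 22 completers per arm, relying on the Sidak-corrected TG pre-post test would show improvement in about 17% of trials with an ineffective programme, against 0.4% for the between-arm test. Correction for multiplicity reduces the excess but cannot cure it, because the within-arm null hypothesis is false whenever scores drift. With no shared gain the excess disappears, so its size depends on assumptions the documents cannot settle, while the need to name the contrast does not. This is a cheap improvement, not a fatal flaw.

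**What to change.** In section 2.9, state that:

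- for each outcome, the programme's effect is judged by the TG-minus-CG difference in change from pre-test to post-test, with its 95% CI: the group-by-time contrast, or a between-arm test of change for non-normal variables;
- the corresponding differences at re-tests 1 and 2 are supportive;
- within-arm changes are descriptive and are not evidence of effect.

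In the Introduction, restate the hypothesis as greater improvement in the TG than in the CG.

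Within-arm p-values need not be banned, provided no claim of benefit rests on them. The cost is wording in two sections, with no added participants or data and no change to the sample size. Section 2.4 says baseline assessments had not begun, so on the article's own account this could be settled before any outcome is seen. The one downside is that within-arm significance can no longer be cited as benefit.

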### 2.3. Sample Size and Power Calculation

The sample size was calculated using RStudio 3.15.0 software (RStudio Inc., Boston, MA, USA) prior to the recruitment of participants. Assuming a study design with a 5% Type I error rate and 75% statistical power, the calculation was informed by effect sizes reported in similar multidomain interventions. These effect sizes were drawn from studies targeting physical, cognitive, and psycho-physiological outcomes in older adults [41,42,43]. A potential 15% dropout rate has been accounted for in the final estimate [44]. This yielded a total sample size of 52 participants (26 per group). While this sample size is considered sufficient to detect meaningful changes, the relatively small cohort may increase the risk of Type II errors. Therefore, upon completion of the trial, the results will have to be interpreted with caution and regarded as preliminary until validated by studies with larger samples.

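### The test for each outcome depends on its observed distribution. With about 22 completers per arm that choice is unstable for moderately skewed outcomes, and it can move an outcome to a branch with no between-arm test of change.

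*Protocol article*

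**What the plan says.** Section 2.9 (Statistical Analysis) sets the task: "Changes within and between the TG and CG from baseline to follow-up assessments will be analyzed using the appropriate tests". It then gives a two-branch rule. The first branch reads "For variables with a normal distribution, a repeated-measures analysis of variance (ANOVA) will be applied", with Sidak-corrected t-tests to follow. The second reads "For non-parametric variables, the Friedman test will be followed by the Wilcoxon test", with a Bonferroni correction. No outcome is assigned to a branch in advance. The Mann–Whitney test is named in the same section, but only for baseline differences.

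The section also states "Group comparisons will adhere to the intention-to-treat principle", prescribes FCS multiple imputation in SPSS, and promises sensitivity analyses "including analyses with and without imputed datasets and potential alternative modeling strategies". It does not say whether the branch is chosen once per outcome or in each imputed dataset.

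Section 2.3 gives 26 participants per group with 15% dropout. Section 2.8 gives four assessments: pre-test, post-test, 3 months and 6 months.

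**The concern.** The distribution of a variable is known only once the data are in, so the data choose the analysis. Three consequences follow.

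- **Instability.** With about 22 completers per arm, a check of normality has limited power. An outcome with mild to moderate skew, which is plausible for timed tests such as TMT, TUG or chair stand, could land in either branch.
- **Different questions.** A repeated-measures ANOVA with group as a factor can test whether change differs between arms. Friedman followed by Wilcoxon compares visits within one arm. The switch can therefore decide whether an outcome keeps its randomised comparison of change.
- **Imputation.** If the rule is applied in each completed dataset, one outcome may fall in different branches across imputations. Friedman and Wilcoxon as named also yield test statistics and p-values, not the estimate and standard error that the usual pooling combines.

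**Working it through.** **1. Sample size per arm.** The article gives 52 in total, 5% type I error, 75% power and 15% dropout, but no effect size, so the calculation cannot be fully reproduced. The dropout step fits: 44 / (1 − 0.15) = 51.8, rounded up to 52. Completers per arm: 26 × 0.85 = 22.1. Each completed dataset under intention to treat holds 26 per arm.

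**2. Cells per outcome.** 2 arms × 4 visits = 8.

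**3. One check in one arm of 22** (Shapiro-Wilk at 5%, 4,000 runs):

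| True shape | Declared non-normal |
|---|---|
| Normal | 5% |
| Lognormal, skewness 0.6 / 0.95 / 1.3 / 1.75 | 15% / 27% / 43% / 57% |
| Lognormal, skewness 2.9 | 81% |
| Exponential | 89% |
| Scale with strong ceiling | about 100% |

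**4. Branch choice over the whole outcome** (22 per arm, 4 visits, within-person correlation 0.7, 1,500 trials; Monte Carlo standard error at most √(0.5 × 0.5 / 1,500) = 1.3 points). Share sent to the rank branch:

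| True shape | All 8 cells must pass | Arms pooled at each visit | Baseline only |
|---|---|---|---|
| Normal | 31% | 17% | 5% |
| Lognormal, CV 0.20 | 67% | 63% | 28% |
| Lognormal, CV 0.30 | 85% | 86% | 52% |

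As a cross-check, eight independent cells would give 1 − (1 − 0.049)^8 = 33% for a normal outcome and 1 − (1 − 0.151)^8 = 73% for skewness 0.6. The correlated results lie a little below, as expected.

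**5. Disagreement between imputed datasets, if normality is judged in each** (26 per arm, 4 missing per arm, correlation with baseline 0.7, 800 runs, checked by arm or pooled). Datasets of the same outcome disagree on the branch in about 7% to 38% of trials with 5 imputations and 14% to 58% with 20. If the branch is chosen once, disagreement is 0%.

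**6. What the rank branch can mislead about** (22 per arm, correlation 0.7, equal change in both arms and so no group effect, 4,000 runs):

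| Change in both arms | Friedman significant in training arm only | Between-arm Mann–Whitney on change |
|---|---|---|
| 0 SD | 4.3% | 4.9% |
| 0.3 SD | 20.7% | 4.5% |
| 0.5 SD | 19.5% | 5.4% |

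A separate simulation with equal change gave 19% to 25% for the training-arm-only pattern.

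**7. Does switching alone inflate error?** With no effect, the all-8-cells rule and CV from 0 to 0.5 (3,000 trials each), the rank branch was chosen in 34% to 99% of trials. Switching between a t-test and a Mann–Whitney test on change gave 4.4% to 5.1% false positives, against 4.5% to 5.1% for always using the t-test.

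**The case against.** Much can be said for the plan. Normality of a variable is common article shorthand, and the choice of check, its unit and its order relative to imputation may sit in an analysis plan that is not shown. Sensitivity analyses with alternative models are promised, and the results are labelled preliminary.

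A reader might also infer four stronger things that the document does not support:

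- **That the choice is a coin toss for every outcome.** Checked by arm, near-normal outcomes stay with ANOVA about 90% to 95% of the time, and strongly skewed or ceiling outcomes go to ranks about 80% to 100% of the time. The Discussion itself expects a possible cognitive ceiling.
- **That checks at this size often reject normal data.** One 5% check does so about 5% of the time. The 31% arises only if all eight cells must pass, a rule the article does not state.
- **That the switch breaks the 5% level.** Step 7 shows no noticeable inflation for like-for-like tests.
- **That rank results cannot be pooled.** Methods exist for combining chi-square statistics across imputations, and Wilcoxon has an associated Hodges–Lehmann estimate. What is true is narrower: the tests as named supply nothing for the usual pooling.

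These limits stand. They do not remove the point, because the switch is a stated rule. An analysis plan that named the check would implement the switch, not abolish it. The preliminary label does not excuse it either, since section 2.9 says type I error control is a priority.

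**Conclusion.** The concern holds in a limited form. The rule makes the analysis unstable for mildly to moderately skewed outcomes: 28% to 67% go to the rank branch at CV 0.20, depending on an unnamed check. Its main cost is that an outcome sent there has no named between-arm test of change. Reading the within-arm tests side by side would show an apparent training-only change in about one trial in five when both arms change equally by 0.3 to 0.5 SD.

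The imputation problem is conditional: disagreement arises only if the branch is judged in each completed dataset. All simulated sizes rest on assumptions: Shapiro-Wilk at 5%, lognormal shapes, correlation 0.7, 4 missing per arm, and 5 or 20 imputations. That the data select the branch, and that the branches differ in what they compare, rests on the text alone. This is a worthwhile, cheap improvement and not a fatal flaw.

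**What to change.** Delete the distribution-dependent switch in section 2.9. Before unblinding:

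- Fix one between-group model for each continuous outcome, with any transformation of the timed tests named in advance.
- Judge the model on its residuals.
- Use the same model in every imputed dataset, and pool its estimate and standard error.
- Run a permutation, bootstrap or rank-based between-arm analysis as sensitivity only.
- Name a suitable between-group method in advance for bounded or ordinal outcomes, such as the 0–12 SPPB score and the three-level Fried class. A transformation will not help these.

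The cost is about a paragraph of wording and a little programming. Section 2.4 says baseline assessments have not begun, so the change can precede all outcome data. The small downside is that effects on log-scale outcomes are reported as ratios.

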## 2. Materials and Methods

### 2.1. Design

This study intends to run an 18-week, two-pronged, parallel, single-blind randomized controlled trial (RCT; ClinicalTrial.gov NCT05481346: https://beta.clinicaltrials.gov/study/NCT05481346 (accessed on 2 August 2022)). It follows the guidelines outlined in the Consolidated Standards for Reporting Trials (CONSORT) recommendations on RCTs [40]. In addition, it adheres to the Standard Protocol Items: Recommendations for Interventional Trials (SPIRIT);both checklist are available in the Supplementary Materials. The research will take place in the sports facilities of the University of Almeria, Spain, and the evaluations will be conducted at the university’s sports science laboratory. Participants have already been selected and are awaiting the commencement of the trial. Prior to the start of the program, participants will be assessed for the pre-test, and then they will proceed to a 2-week familiarization program.

To ensure participant safety during the outdoor training, a comprehensive plan will be implemented, with all instructors trained in basic first aid and emergency response protocols. In case of injury or medical emergency, participants will be referred to medical professionals, and emergency contacts will be available. Weather-related challenges will be managed with real-time weather monitoring; sessions will be rescheduled if adverse conditions (e.g., extreme heat, rain, or storms) are predicted. Participants will be informed of weather conditions and provided with guidelines on appropriate attire.

In accordance with SPIRIT Item 13, Table 1 presents the schedule of enrolment, interventions, and assessments.

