	Frailty	Fried questionnaire	The Fried questionnaire evaluates five criteria related to frailty: involuntary weight loss, exhaustion, weakness, slow gait speed, and low physical activity. The number of criteria met is classified as a three-level variable representing robustness (0 criteria met), pre-frailty (1 or 2 criteria met), and frailty (3 or more criteria met) [15].
	Emotional state	Centre for Epidemiological Studies Depression Scale-Revised (CESD-R)	The CESD-R is a 20-item questionnaire that measures depressive symptoms among older participants. Participants indicate the number of days on which they experienced depressive symptoms during the previous week using a standard four-point Likert scale. Higher scores indicate more depressive symptoms [16].
		Perceived Stress Questionnaire (PSQ)	The Perceived Stress Questionnaire (PSQ) is a psychological tool used to assess an individual’s subjective perception of stress in their daily life, focusing on feelings, thoughts, and reactions to stressful situations [17].
		Emotional intelligence in adults (EQ-i-M20)	The EQ-i-M20 is a 20-item questionnaire with subcategories such as intrapersonal, interpersonal, stress management, adaptability, and general mood [18].
	Satisfaction with life	Satisfaction with Life Scale (SWL)	The scale consists of four items rated on a Likert-type scale, ranging from 1 to 7, which assesses global subjective happiness [19].
	(e) Motivation	Behavioral Regulation during Exercise Questionnaire-3 (BREQ-3)	The BREQ-3 will be used to assess motivational regulation related to physical exercise. The questionnaire consists of twenty-three items distributed across three dimensions based on the Self-Determination Theory (SDT), which distinguishes between autonomous motivation, controlled motivation, and amotivation [20].

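### For non-normal outcomes, section 2.9 promises a between-group analysis but names only within-participant tests (Friedman, then Wilcoxon), which cannot test TG against CG

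*Protocol article*

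**What the plan says.** The trial is a randomised two-arm comparison (section 2.1): "This study intends to run an 18-week, two-pronged, parallel, single-blind randomized controlled trial". Section 2.9 states the aim of the outcome analysis: "Changes within and between the TG and CG from baseline to follow-up assessments will be analyzed using the appropriate tests". It then splits outcomes by distribution.

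- Normal outcomes: "For variables with a normal distribution, a repeated-measures analysis of variance (ANOVA) will be applied". Post hoc t-tests with Sidak correction follow.
- Other outcomes: "For non-parametric variables, the Friedman test will be followed by the Wilcoxon test, with the Bonferroni correction applied for multiple comparisons".

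The only two-sample rank test in the section is reserved for baseline: "To assess baseline characteristic differences between groups, the Student’s *t*-test will be used for parametric numerical variables, the Mann–Whitney U test for non-parametric variables". Section 2.9 also says "Group comparisons will adhere to the intention-to-treat principle", and describes the sensitivity analyses as "including analyses with and without imputed datasets and potential alternative modeling strategies". It does not say which outcomes are expected to be non-normal, nor whether Friedman is to be run in each arm or over both arms together.

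**The concern.** The question a randomised trial answers is whether TG changed more than CG. Friedman asks whether the visits differ within people, and a Wilcoxon test used as its follow-up asks which pair of visits differs. Run in each arm, the rule invites a comparison of significant in TG with not significant in CG, which is not a test of the difference. Run over both arms together, it ignores allocation.

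All participants are assessed four times (sections 2.6 and 2.8), so a shared gain from practice is a natural possibility, particularly on timed cognitive tests. Plausible candidates for the non-normal route are Trail Making and Stroop times and the 0–12 SPPB score, which Table 3 lists as primary evaluations, and CESD-R and the frailty class, which it lists as secondary. The frailty class is ordinal by construction: "The number of criteria met is classified as a three-level variable representing robustness", with pre-frailty and frailty as the other two levels. The Discussion itself expects a possible ceiling effect in cognitive outcomes, which makes non-normality there more likely but does not establish it.

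**Working it through.** **What the named tests compute.** The plan gives no figure on this point, so the first step is structural. With *n* people and *k* visits, Friedman ranks each person's own *k* values and sums the ranks by visit, *R_j*:

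Q = 12 / (n·k·(k+1)) × Σ R_j² − 3·n·(k+1)

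With k = 4 this is Q = 12/(20n) × Σ R_j² − 15n. Nothing in it depends on arm. The signed-rank test uses the differences between two visits in the same person, and again arm does not enter. Wilcoxon can also mean the two-sample rank-sum test, but section 2.9 calls that test Mann–Whitney U, and the usual follow-up to Friedman is the signed-rank test.

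**Stated sample size.** Section 2.3 gives 52 in total (26 per group) at 5% type I error, 75% power and 15% dropout, but no effect size, so it cannot be reproduced directly. Assuming a standardised difference of 0.8 and a two-sided two-sample comparison, n = 22 per arm and 44/0.85 = 51.8, rounded up to 52. This neither supports nor refutes the point. It only shows that 52 is compatible with a two-sample comparison, which the non-normal rule does not make.

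**Illustration by simulation.** From the article: four visits, 1:1 allocation, 26 per arm, 15% dropout, so 26 × 0.85 = 22.1, taken as 22 per arm. Assumed: normal data without ties, within-person correlation 0.7, no treatment effect, and the same gain in both arms at every post-baseline visit. Also assumed is the Bonferroni divisor, which the article does not give: four visits make 4 × 3 / 2 = 6 pairs, so the threshold is 0.05/6 = 0.0083. The rule counts as significant when Friedman gives p < 0.05 and the pre–post signed-rank test then gives p < 0.0083.

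| Result, no treatment effect | Shared gain 0.3 SD | Shared gain 0.4 SD |
|---|---|---|
| Significant in TG | about 13% | about 29% |
| Significant in TG but not CG | about 12% | about 20% |
| Significant, arms pooled | about 37% | about 68% |
| Mann–Whitney on pre–post change, TG v CG | about 5% | about 5% |

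Repeat runs of 3,000 to 4,000 trials move these figures by one or two percentage points. As a check on the TG-only row, the arms are independent, so the expected share is p(1 − p): 0.13 × 0.87 = 0.11 and 0.29 × 0.71 = 0.21.

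**Other assumptions.** With log-normal data, 26 per arm and correlation 0.6, shared shifts of 0.3, 0.5 and 0.7 latent SD give TG-only significance in 9%, 24% and 17% of trials and pooled significance in 29%, 82% and 99%. Mann–Whitney on change stays at 5.4%, 4.9% and 4.8%. The error also runs the other way: with true shifts of −0.4 in CG and +0.4 in TG, the pooled rule is significant in 0.3% of trials and the between-arm test in 82%.

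**The case against.** The strongest reply is that section 2.9 plainly intends to compare groups: it says so, it applies intention to treat to group comparisons, and it leaves room for alternative models in sensitivity analyses. A reader might infer that non-normal outcomes will receive no between-group comparison at all and that randomisation goes unused. The article does not support that. It supports only that the tests it names cannot make the comparison it promises. The reply does not remove this mismatch, because declared intent is not a test and unspecified sensitivity models do not supply the main analysis. Nor is this detail left to a fuller plan, since the article itself fixes the tests.

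Three further limits stand.

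- A reader might infer that the primary cognitive outcomes are affected. The article does not say which outcomes will be non-normal. Those judged normal go to repeated-measures ANOVA, which can carry a group-by-time term.
- It is too strong to say that practice gains would be taken for benefit. CG takes the same tests at the same visits and both arms are described at each, so a shared gain would be visible. That it could be misread is supportable.
- Friedman alone gives larger figures: at 0.3 SD, about 31% in TG, 21% in TG only and 62% pooled. These leave out the corrected Wilcoxon step and so do not describe the rule as written.

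The study is also described as preliminary and exploratory, with results to be read cautiously. This tempers the consequence, but the plan still sets a significance threshold of 0.05 and hypothesises significant improvements.

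**Conclusion.** The point holds as a contradiction within section 2.9: a between-group analysis of change is promised, and the tests named for non-normal outcomes compare visits within participants. This follows from the definition of the tests and rests on no numerical assumption. Its practical size does depend on assumptions. For a shared gain of 0.3 to 0.4 SD and no treatment effect, a TG-only finding would arise in roughly one trial in eight to one in five for each outcome analysed this way, while a between-arm rank test holds its 5% level. The gain, the correlation, the absence of ties and the divisor of 6 are all assumed. SPPB and the frailty class would be heavily tied, so the percentages should not be carried over to them. How many outcomes are affected cannot be read from the article.

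**What to change.** Name, for every outcome that is not analysed by repeated-measures ANOVA, a between-arm analysis on which conclusions will rest. Suitable choices are rank ANCOVA or a transformed-scale model with baseline as covariate for skewed measures such as test times, and an ordinal model for SPPB and the frailty class. The minimum that closes the gap is Mann–Whitney U on change from baseline, TG against CG; adjusting for baseline is preferable but is not required to resolve the contradiction. Keep Friedman and Wilcoxon within each arm as description, and state that significance in one arm and not in the other is not evidence of a treatment effect.

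The cost is a few lines of text and standard software syntax, with no extra data or participant burden. According to section 2.4, baseline assessments and the intervention had not begun, so on the article's account the change can be made before any outcome data exist.
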